## Abstract

Emotional Disorders (EDs) are very prevalent in Primary Care (PC). However, general practitioners (GPs) have difficulties to make the diagnosis and the treatment of this disorders that are usually treated with drugs. Brief psychological therapies may be a new option to treat EDs in a PC context. This article aims to present a study protocol to evaluate the effectiveness and the efficiency of an adaptation to brief format of the “Unified Protocol (UP) for the transdiagnostic treatment of EDs.” This is a single-blinded RCT among 165 patients with EDs. Patients will be randomly assigned to receive brief psychological treatment based on UP, conventional psychological treatment, conventional psychological treatment plus pharmacological treatment, minimum intervention based on basic psychoeducational information, or pharmacological treatment only. Outcome measure will be the following: GAD-7, STAI, PHQ-9, BDI-II, PHQ-15, PHQ-PD, and BSI-18. Assessments will be carried out by blinded raters at baseline, after the treatment and 6-month follow-up. The findings of this RCT may encourage the implementation of brief therapies in the PC context, what would lead to the decongestion of the public health system, the treatment of a greater number of people with EDs in a shorter time, the reduction of the side effects of pharmacological treatment and a possible economic savings for public purse.

**Clinical Trial Registration:**
ClinicalTrial.gov, identifier NCT03286881. Registered September 19, 2017.

## Introduction

### Background

Nowadays, concern for mental health disorders and problems has increased significantly worldwide (Mental Health Foundation, 2016). Common mental health disorders, also called emotional disorders (EDs), are growing exponentially in recent decades (Vos et al., 2015; Chisholm et al., 2016). These disorders include DSM-5 (American Psychiatric Association, 2013) diagnostics of depression, generalized anxiety disorder, panic disorder, obsessive-compulsive disorder, post-traumatic stress disorder, social anxiety disorder, and specific phobias (National Institute for Health, and Clinical Excellence [NICE], 2011). EDs are very prevalent in primary care (PC) services (Roca et al., 2009; Lejtzén et al., 2014), since about 40% PC consultations would be direct or indirect related with this kind of problems (Kroenke et al., 2007).

Some researches point out the difficulties presented by general practitioners (GPs) to make the diagnosis and the treatment of EDs (Collings, 2005; Aragonés et al., 2006; Fernández et al., 2006; DeVicente and Berdullas, 2009; Gerrits et al., 2013; Jacka et al., 2013), and warn of the excess in the use of drugs (Secades Villa et al., 2003). Patients with mild-moderate symptoms of EDs are usually treated in PC with drugs as the first therapeutic option (Kovess-Masfety et al., 2007), which contradicts the research and the international clinical guides instructions (National Institute for Health, and Clinical Excellence [NICE], 2011), that suggest psychological therapies as treatment of choice. Although pharmacological treatment is obviously of choice in severe cases, scientific research indicates that many of the patients with mild-moderate symptoms could reduce them with psychological treatments, without medication (Moreno and Moriana, 2012) and that psychological treatment is more effective than medication in these patients in a PC context (Watts et al., 2015). In the same way, it is suggested that, independently of the severity of the case, psychological treatment should always be present (Gonçalves et al., 2003; National Institute for Health, and Clinical Excellence [NICE], 2011). Other studies have concluded that psychological treatment applied in PC for this kind of patients promotes a greater recovery, improves the quality of care, decreases the prescription of drugs and reduces the hyperfrequency (Wells et al., 2000; Patel et al., 2010). Furthermore, psychological treatment is mostly preferred by patients, since it is in accordance with their conception of the problems they suffer (Prins et al., 2008; Walters et al., 2008).

Despite the importance of evaluating the efficacy of psychological treatments (Moriana et al., 2017; Gálvez-Lara et al., 2018), the knowledge of the empirical research’s results and its later integration by the professional in the clinical practice does not get to consolidate completely in the applied fields (Herbert, 2003; Kazdin, 2008, 2011; Barlow et al., 2013). In this line, some studies have evidenced that psychologist, often, do not use evidence-based treatment (Lilienfeld, 2010; Dobson and Beshai, 2013; Dozois, 2013). At other times, psychologists do not use all the key elements of evidence-based treatment (Stobie et al., 2007). For these reasons, some authors have manifested the existence of a gap between the applied psychology and the scientific research (Westen et al., 2004; Kazdin, 2008, 2011; Babione, 2010).

Some surveys have indicated that applied psychologists feel that research’s findings do not show the reality of clinical practice (Tasca et al., 2015) and affirm that the manualized treatments are very rigid for the habitual clinical practice (Gyani et al., 2015). This situation has promoted the demand for a better adequacy of the treatments to the real contexts of application (Kazdin, 2008), which entails their flexibility and use in different contexts (primary and specialized care) and their adaptation to brief formats of limited time (Moriana and Martínez, 2011).

### Brief Therapies: Adaptation of the Psychological Treatments to the Real Context of Application

In recent years, the possibility of adapting conventional psychological therapies to an abbreviated format as a possible solution for the correct treatment of EDs has been suggested (Shepardson et al., 2016). Brief therapy or “time limited therapy” emerges as a therapeutic option of low cost to respond to the demands of public health about the use of psychological therapies of short duration that generate favorable results in clinical practice (Hewitt and Gantiva, 2009). To be considered short, a therapy should have more than two sessions and less than ten, establishing an average of six sessions, on the basis of the idea that the guides are flexible to the characteristics and symptoms of the patient (Cape et al., 2010). Although there is no agreement among different authors about how many sessions include limited time therapies, all agree on the importance of the time as a therapeutic tool (Miller, 2000; MacNeil, 2001; Bedics et al., 2005; Hewitt and Gantiva, 2009; Lyons and Low, 2009). The limitation of the number of sessions helps both therapist and patient to focus fully on the therapy, increases the motivation of the patient and requires the establishment of achievable goals by the professional, considering each session as one intervention with a particular outcome with the aim that the patient undergoes change as soon as possible (Fosha, 2004).

Brief therapy responds adequately to the economic resources and psychological requirements of patients (Lyons and Low, 2009), and could be used to offer psychological therapy to patients who are in waiting lists for access to specialized programs, such as initial treatment for risk users and as a complement to more extensive psychological treatments (Sánchez and Gradolí, 2002). Due to its idiosyncrasy, brief therapies are especially indicated for adaptive and emotional problems of mild or moderate severity and it is suggested that they should be the first step for the therapeutic approach in this patient profile, giving a wide accessibility to patients and an effective response to their symptoms (Collings et al., 2015).

Some works have shown that brief therapies have obtained similar results to conventional therapies (Miller, 2000; Bloom, 2001; Lyons and Low, 2009; Nieuwsma et al., 2012), demonstrating its effectiveness in reducing anxiety and depressive symptoms (Koutra et al., 2010; Bernhardsdottir et al., 2013; Saravanan et al., 2017), on the improvement of problem-solving skills (Bannink, 2007), in reducing symptoms of posttraumatic stress disorder (Kip et al., 2016) or in the decrease in the intake of alcohol in people who had an excessive consumption (Gantiva et al., 2003). In addition, brief therapies have not only proved effective immediately after treatment, but also that the improvement in the patient stays long after the end of the intervention (Hamdan-Mansour et al., 2009; Vázquez et al., 2012).

### Unified Protocol for the Transdiagnostic Treatment of EDs

One of the main problems of the categorical approach to psychopathology is the high comorbidity among the different mental disorders (Sandín et al., 2012). In last years, a new approach has emerged for the treatment of mental disorders that aims to develop interventions that can be used to treat the common symptoms of various psychological disorders (Belloch, 2012). This approach, known as transdiagnostic, considers that mental disorders share numerous cognitive and behavioral processes that contribute to the development and maintenance of symptoms (Harvey et al., 2004). Thus, the transdiagnostic treatment is defined as a “therapy that is made available to individuals with a wide range of diagnosis and that does not rely on knowledge of these diagnoses to operate effectively” (Mansell et al., 2009, p. 14).

Psychological treatment from a transdiagnostic approach is especially appropriate for EDs, since accumulated finding have shown important shared characteristics among depression, anxiety, and other emotion-related disorders (Barlow, 2002; Barlow et al., 2004; Brown and Barlow, 2009; Rosellini et al., 2015). David Barlow and their team developed the “Unified Protocol for the transdiagnostic treatment of EDs” to address the underlying symptoms of disorders in which anxiety and emotional deregulation play an important role (Allen et al., 2008; Ellard et al., 2010; Barlow et al., 2011). The efficacy of PU has been widely demonstrated (Reinholt and Krogh, 2014), both in individual format (Farchione et al., 2012) as in group format (Bullis et al., 2015), with the possibility of simultaneous application to patients with a variety of disorders, so it could reduce the waiting lists and the cost of the individual treatment (Osma et al., 2018).

From a transdiagnostic perspective focused on brief therapies (less than ten session) for the treatment of the EDs, several studies have shown their effectiveness both for the reduction of symptoms and for the application of treatment to many patients with different characteristics and comorbid disorders (Roy-Byrne et al., 2010; Dear et al., 2011; Titov et al., 2011; Schmidt et al., 2012; Osma et al., 2015). However, these studies present some limitations related to their designs, since some of them lack a control group (single group design), and others use only a waitlist control group or medication (treatment as usual) as a comparator.

Due to the limitations of the previous studies, it is necessary to design a protocol that evaluates the efficacy of brief therapy from a transdiagnostic perspective compared to other treatment modalities that are frequently used in mental health services (e.g., conventional psychological treatment, combined treatment or psychoeducational information).

### The Present Study

The aim of this work is to examine the efficacy of several types of interventions, in therapeutic and cost-effectiveness terms, for the treatment of patients with EDs. The different interventions are the following: brief psychological treatment based on UP; conventional psychological treatment; conventional psychological treatment plus pharmacological treatment; minimum intervention based on basic psychoeducational information, counseling and bibliotherapy; and pharmacological treatment.

We hypothesize that “conventional psychological treatment plus pharmacological treatment” will be the most effective treatment, but “brief psychological treatment based on UP” will be the most efficient treatment (cost-effectiveness). Besides, we expect that psychological treatment (brief and conventional) will be more effective than pharmacological treatment, but less effective than “conventional psychological treatment plus pharmacological treatment,” and that “brief psychological treatment” will be as effective as “conventional psychological treatment” but more efficient than this one. Finally, we think that “minimum intervention based on basic psychoeducational information, counseling, and bibliotherapy” will be more effective than pharmacological treatment but will get worst results that different versions of psychological treatment.

## Materials and Equipment

### Study Design

This will be a multicenter randomized controlled trial (RCT) with five groups that will be realized in primary and specialized care centers from Córdoba (Spain) and its province. Patients will be randomly assigned to receive one of the following interventions: (a) *Brief psychological treatment based on UP*, (b) *Conventional psychological treatment*, (c) *Conventional psychological treatment plus pharmacological treatment*, (d) *Minimum intervention based on basic psychoeducational information, counseling and bibliotherapy*, and (e) *Active comparator treatment as usual (TAU): pharmacological treatment only*. For ethical reasons, in the case of low response to treatment, participants in the *Brief psychological treatment* and *Minimum intervention conditions* will be removed from the trial and will receive the treatment proposed by their GP. Outcome measures will be taken before randomization (baseline assessment), after the intervention (post-treatment assessment) and at 6-month follow-up. The overall study design is summarized in Figure 1. This RCT will be implemented following the SPIRIT guidelines (Chan et al., 2013a,b) and the CONSORT statement (Moher et al., 2010; Schulz et al., 2010).

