### Interventions

#### Brief Psychological Treatment Based on UP

This intervention protocol consists of eight sessions according to an adaptation to brief format of the UP for the transdiagnostic treatment of EDs (Boisseau et al., 2010; Ellard et al., 2010; Barlow et al., 2011) and the NICE guideline “*Common mental health disorders”* (National Institute for Health, and Clinical Excellence [NICE], 2011). The treatment is developed by clinical psychologists in Specialized Care (SC). Each session has specific objectives:

S1.*Motivation for change and commitment to treatment*. The aim of the first session is to improve motivation for change analyzing the advantages and disadvantages of changing and defining determinants life goals.S2.*Understanding the function of emotions*. The second session gives information regarding the adaptive functions of emotions, introduces the concept of Emotion Driven Behaviors (EDBs) and distinguishes between thoughts, physical sensations and behaviors related to emotions.S3.*Emotional awareness training*. The third session aims to introduce and to practice emotional awareness centered on the present, without judging.S1.*Cognitive appraisal*. The objective of the fourth session is to teach appropriate thinking patterns, showing how to identify maladaptive ways of thinking and how to modify them.S4.*Emotional avoidance and EDBs*. The purposes of this session are to teach patients that emotional avoidance strategies favor the development and maintenance of EDs and help them to change their own maladaptive behaviors for others more appropriate and functional.S5.*Tolerance to physical sensations*. This session aims for the patient to get used to the physical sensations by performing exercises that causes these physical sensations, such as breathing through a straw.S6.*Interoceptive and situational emotional exposure*. The main of this session is to expose the patient to internal and external triggers that produce intense emotional reactions, in order to improve the habituation to emotions and decrease avoidance behavior.S7.*Conclusion and relapse prevention*. The objectives are to discuss the skills learned throughout the treatment, to identify the skills that should continue to be practiced in the future and to instruct how to face future situations.

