## Proposed Analysis

The data will be analyzed following both intention-to-treat (ITT) and per protocol approaches. Firstly, ANOVA or chi-squared will be performed to compare the demographic variables and outcomes measures at baseline. Second, to examine longitudinal changes over time (baseline, posttreatment and follow-up) and between-group differences on these changes we will use linear mixed models, inasmuch as these models are more accurate than repeated-measures ANOVAs (Gueorguieva and Krystal, 2004). In the ITT analysis (all patients randomized are included in the analysis), the incomplete or missing data will be considered using the maximum likelihood estimation method. Additionally, Cohen’s *d* will be calculated to determine the size of between-group effects. Last, we will estimate the Incremental Cost-Effectiveness Ratio (ICER) to compare the relationship between costs and effectiveness of different interventions.

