## Limitations

This study presents several limitations. The first one is related to the design of the study, since the interventions included in the protocol are composed by a different number of sessions. Nevertheless, it is necessary to include interventions with different length to determine whether the treatment effect varies depending on the intensity and duration. Besides, except for the “brief psychological treatment based on UP” group, the number of sessions or weeks of interventions within a certain group could vary from one patient to another. However, we will make sure that each patient is evaluated 6 months after the end of the treatment (follow-up assessment).

As a limitation inherent in this type of studies, considerable dropout rate during the intervention process are expected, as well as a substantial missing data to follow-up. Nevertheless, participants will be animated by phone or email to continue with the treatment or to participate in the follow-up assessment. In addition, the anxious-depressive symptoms could be attenuated by the passage of time.

Other limitations may be related to the recruitment difficulties. Due to the participants must be diagnosed with a DSM-5 disorder and must meet predetermined cutoff points, may be recruitment problems related to the difficulty that participants completely met the eligibility criteria. Besides, patients may refuse to be treated by a different intervention than usual.

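### Removing low responders from the trial in the brief and minimum arms only must be reconciled with the ITT, follow-up and ICER plans; if removal ends data collection, those arms' costs are understated.

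*Protocol article*

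**What the plan says.** The Study Design section of the protocol article states that, for ethical reasons, participants with a low response in the brief psychological arm and the minimum-intervention arm "will be removed from the trial and will receive the treatment proposed by their GP". The sentence names those two arms only. No equivalent is stated for the conventional, combined or TAU arms, whose treatment may run for up to 8 months.

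Four other statements bear on what happens to these patients:

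- Proposed Analysis, analysis sets: "The data will be analyzed following both intention-to-treat (ITT) and per protocol approaches". The ITT set is defined so that "all patients randomized are included in the analysis", and within it "the incomplete or missing data will be considered using the maximum likelihood estimation method".
- Proposed Analysis, economics: "we will estimate the Incremental Cost-Effectiveness Ratio (ICER) to compare the relationship between costs and effectiveness of different interventions". The article says nothing more about costing.
- The Present Study: the brief arm is expected to be the winner on efficiency; it "will be the most efficient treatment (cost-effectiveness").
- Limitations: "we will make sure that each patient is evaluated 6 months after the end of the treatment (follow-up assessment").

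**The concern.** The removal rule depends on outcome and applies to two of five arms. One of those two is the arm predicted to be the most efficient. Read at face value, a patient removed from the trial is no longer observed, yet the health service goes on to pay for whatever the GP proposes. Such a patient would add only the sessions used before removal to the brief or minimum arm's cost. A non-responder in the conventional, combined or TAU arm has no such exit and goes on generating observed cost for as long as he or she stays in treatment. Recorded cost in the two low-intensity arms would then fall as failures rise.

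This is separate from missing symptom scores. Maximum likelihood is described for incomplete data in the ITT analysis, without mention of costs, and it cannot recover the cost of a different treatment that nobody recorded. The per-protocol analysis may drop the failures altogether.

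At stake are the efficiency hypothesis and the suggestion of public savings in the Conclusion.

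**Working it through.** **The passages side by side.** Removal from the trial on low response (Study Design), inclusion of every randomised patient (Proposed Analysis) and assessment of each patient 6 months after treatment ends (Limitations) fit together only if removal means stopping the assigned treatment while data collection continues. The article does not say so. It also does not say when treatment ends for a removed patient, so the timing of that patient's assessments is undefined.

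**Size of the cost effect.** The article gives no cost or ICER figure to reproduce, so sessions serve as a proxy.

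Inputs from the article:
- brief arm: 8 sessions ("This intervention protocol consists of eight sessions");
- conventional arm: 12 to 24 sessions, midpoint 18;
- minimum arm: 2 to 5 GP sessions.

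Assumptions, none of them in the article: a share r of brief patients is removed after 4 sessions, and each then receives 18 conventional sessions.

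- Counted sessions per brief patient = 8(1 − r) + 4r = 8 − 4r
- Incurred sessions = 8 − 4r + 18r = 8 + 14r
- Share missed = 18r / (8 + 14r)

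| r | Counted | Incurred | Missed | Apparent saving vs 18 | Saving with full counting |
|---|---|---|---|---|---|
| 10% | 7.6 | 9.4 | 1.8/9.4 = 19% | 10.4 | 8.6 |
| 30% | 6.8 | 12.2 | 5.4/12.2 = 44% | 11.2 | 5.8 |
| 40% | 6.4 | 13.6 | 7.2/13.6 = 53% | 11.6 | 4.4 |

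The apparent saving grows with the failure rate while the saving with full counting shrinks.

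**Sensitivity to the assumptions.** Suppose instead that all 8 sessions are used before step-up, and that a share p then receives C conventional sessions. Incurred sessions are 8 + pC, and the share missed is pC / (8 + pC).

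| p | C = 12 | C = 18 | C = 24 |
|---|---|---|---|
| 20% | 10.4 (23% missed) | 11.6 (31%) | 12.8 (38%) |
| 40% | 12.8 (38%) | 15.2 (47%) | 17.6 (55%) |

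**Does the ranking against conventional treatment change?** Under the first set of assumptions, brief stays below 18 sessions until 8 + 14r = 18, that is r = 10/14 = 71%. Under the second, the break-even is p = (C − 8)/C: 33% for C = 12, 56% for C = 18 and 67% for C = 24. Below these rates brief still uses fewer sessions after full counting.

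**Brief against minimum.** The minimum arm has the same removal rule and fewer sessions. Even with step-up left out, brief counts 8 − 4(0.4) = 6.4 sessions at 40% removal, against at most 5 for minimum. The omission does not put brief ahead.

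**If the GP proposes drugs.** No psychologist sessions are missed. What goes uncounted is GP contacts (the TAU section describes consultations of 5 to 7 minutes) and prescriptions. The article gives no unit costs, so this amount cannot be computed, but in session terms it is far smaller than in the tables.

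**The case against.** The strongest reply is that the article contains no costing rule that could be wrong. It announces an ICER and leaves cost source, perspective and horizon open, as a journal article may. The ITT definition and the promise to assess each patient suggest that removed patients are kept. Later contacts could also be read from health-service records, so leaving trial visits need not mean losing costs. Drug treatment is the usual GP response as the article itself describes it, which makes 18 specialist sessions an unfavourable pathway to assume.

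Much of this stands, and it rules out three stronger readings that a reader might infer:

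- That step-up cost is never charged to the brief and minimum arms. No passage says so; the article is silent.
- That the cost window differs by arm because follow-up runs from each patient's own end of treatment. The Limitations section times an outcome assessment there and defines no window for costs.
- That the efficiency result is built in. The break-even rates above show that brief can remain cheaper than conventional with everything counted, and minimum benefits from the same rule. An ICER also depends on effects, which session counts do not address.

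The reply does not dispose of the removal rule. That rule is stated, one-sided and dependent on outcome. No later analysis plan can cost care that was not recorded, and the passages that point towards retention contradict the plain meaning of removal from the trial.

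**Conclusion.** The concern holds as a contradiction that must be resolved, with a conditional bias attached. If removal ends data collection, as its wording suggests, the cost and outcome of later care are lost for treatment failures in the brief and minimum arms only. Their cost is then understated relative to the conventional, combined and TAU arms, and the cost comparison leans towards the hypothesised efficiency of brief treatment.

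The size depends on the removal rate, the unit costs and the type of care the GP proposes, none of which the article states. Where step-up is to conventional therapy, the session illustrations put the understatement at roughly a fifth to a half of the arm's use; where it is to drugs, much lower. The direction against the three arms without the rule is clear. A change in ranking is not shown. The point should be settled before data collection, because resource use not collected at the time may be hard to recover.

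**What to change.** Leave the clinical step-up rule as it is and change what it means for the data:

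1. In Study Design, define low response as stopping the assigned treatment, not as leaving the trial, and bring this into line with the ITT definition and the follow-up statement. Say when treatment is taken to end for such a patient.
2. Keep collecting outcomes at the planned assessments for all randomised patients. Collect resource use for them too, taking contacts and prescriptions from service records.
3. In Proposed Analysis, run the primary ICER by randomised arm, with step-up care charged to that arm.
4. Measure costs and effects over the same stated horizon from randomisation. Extending the cost horizon alone would charge step-up care without crediting its benefit. Because assessments are timed from each patient's end of treatment, the horizon has to be one at which outcomes are available; a fixed-time assessment may be needed.
5. Report the cost of assigned treatment alone as a secondary figure.

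The cost is a change of wording, some record extraction for patients who stop early, and possibly that one assessment. The brief and minimum arms will look less cheap than they would with step-up care left out.
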